**End term evaluation: The entire above plus**

| **Q-Number** | **Question** | **Response** | **Code** |
| --- | --- | --- | --- |
| **Blood Lipids** | | | |
| 132. | What is the number of healthy plates consumed on average per week? | _______ | Qn132 |

**Socio-economic and cultural factors which may impend uptake and adherence to healthy plate**

| **Q-Number** | **Question** | **Response** | **Code** |
| --- | --- | --- | --- |
| **Blood Lipids** | | | |
| 133. | Based on your experience do you think are some financial issues which from not consuming healthy plate? |  | Qn133 |
| 134. | In this place do you think there some cultural factors which may hinder you from not consuming healthy plate? |  | Qn134 |
| 135. | If yes, what are those factors? |  | Qn135 |
| 136. | What do you recommend towards improving availability, affordability and accessibility of healthy plate from the street food vendors? |  |  |
|  | 1. Availability: |  | Qn136a |
|  | 1. Affordability: |  | Qn136b |
|  | 1. Accessibility: |  | Qn136c |

**Ufanisi wa kipengele cha kinga na mwongozo kwa ajili ya kubaini vimeng’enywa hatarishi vya aina ya pili ya ugonjwa wa kisukari miongoni mwa walaji wa vyakula vilivyopikwa vya mitaani nchini Tanzania: Jaribio la utafiti**

**Sehemu A: Taarifa za utambulisho**

| **Namba ya swali** | **Swali** | **Jibu** | **Code** |
| --- | --- | --- | --- |
| 1. | Wilaya: 1. Ilala 2. Kinondoni 3. Ubungo |  | Qn1 |
| 2. | Jina la soko: |  | Qn2 |
| 3. | Aina ya soko kwenye utafiti: 1. Jaribio 2. Siyo jaribio |  | Qn3 |
| 4. | Majina ya mhojaji (vifupi):_______________ |  | Qn4 |
| 5. | Tarehe ya mahojiano______________________ |  | Qn5 |
| 6. | Fomu ya ridhaa imesomwa na ridhaa imepatikana?   1. Ndiyo 2. Hapana |  | Qn6 |
| 7. | Muda wa kuanza mahojiano (kwa masaa 24)_______________ |  | Qn7 |
| 8. | Muda wa kumaliza mahojiano (kwa masaa 24)______________ |  | Qn8 |
| 9. | Jina la ukoo______________________________ |  | Qn9 |
| 10. | Jina la kwanza____________________________ |  | Qn10 |
| 11. | Namba ya simu:___________________________ |  | Qn11 |
| 12. | Mmiliki wa simu: 1. Ya ofisini 2. Nyumbani  3. Jirani 4. Nyingine___________ |  | Qn12 |

**Sehemu B: Step 1: Taarifa za kidemographia**

| **Namba ya swali** | **Swali** | **Jibu** | **Code** |
| --- | --- | --- | --- |
| 13. | Jinsi: 1. Me 2. Ke |  | Qn13 |
| 14. | Tarehe ya kuzaliwa? DD/MM/YYYY______________________  *Sijui 77 77 7777* |  | Qn14 |
| 15. | Una umri gani? |  | Qn15 |
| 16. | Kwa jumla, umetumia miaka mingapi shuleni au katika masomo yako mpaka sasa (ukiondoa muda wa kabla ya shule ya msingi)?  ____________________________ |  | Qn16 |
| 17. | Elimu yako ya juu uliyofikia : 1. Hana 2. Msingi  3. Sekondari 4. Chuo |  | Qn17 |
| 18. | Hali ya ndoa? 1. Mseja 2. Ameoa/olewa  3. Wametengana 4. Mtalaka  5. Mjane/mgane 6. Wanaishi pamoja |  | Qn18 |
| 19. | Ni chanzo chako kikuu cha kipato kwa kipindi cha miezi 12 iliyopita?  1. Mwajiriwa wa serikali 2. Mwajiriwa siyo wa serikali  3. Ajira binafsi 4.Ajira bila malipo  5. Kazi za nyumbani 6. Mstaafu  7. Hana ajira (aweza kufanya kazi)  8. Hana ajira (hawezi kufanya kazi)  9. Kakataa kujibu |  | Qn19 |
| 20. | Katika kaya yako kuna watu wangapi wenye umri wa kuanzia miaka 18 na kuendelewa ikiwepo na wewe?  ________________ |  | Qn20 |
| 21. | Kwa mwaka jana, waweza niambia kwa wastani kaya yako ilikuwa inaingiza kipato kiasi gani kwa:   1. Siku______________________________________ 2. Wiki______________________________________ 3. Mwezi_____________________________________ 4. Mwaka_______________________________________ |  | Qn21a  Qn21b  Qn21c  Qn21d |

**Sehemu D: Step 1: Mtazamo kuhusu kuishi maisha ya afya ili kujikinga na ugonjwa wa kisukari**

| **Namba ya swali** | **Sentensi** | **Jibu** | **Code** |
| --- | --- | --- | --- |
|  |  | 1.Nakubali kabisa  2.Nakubali  3.Sikubali  4.Nakubali kabisa |  |
| 22. | Inawezekana kuzuia kisukari cha aina ya pili kwa ulaji unaozingatia afya |  | Qn22 |
| 23. | Historia ya familia ya ugonjwa wa kisukari ina mchango kwa mtu kuishi maisha ya taadhari |  | Qn23 |
| 24. | Kitambi kinaongeza hatari ya kupata ugonjwa wa kisukari |  | Qn24 |
| 25. | Kufanya mazoezi mara kwa mara kunaitaji juhudi nyingi |  | Qn25 |
| 26. | Kila mtu anapaswa kuwa mwangalifu kujikinga na kisukari kadiri umri wake unavyoongezeka |  | Qn26 |
| 27. | Kama kuna uwezekano mkubwa wa kupatatwa na kisukari mfano kuwa na historia ya kisukari ndani ya familia kunakuwa hakuna jinsi ya kufanya ili kujikinga au kuchelewesha kupata kisukari |  | Qn27 |
| 28. | Ukijaribu unaweza kupunguza uwezekano wa kupata Kisukari |  | Qn28 |
| 29. | Watu wanaochukua hatua wanaweza kupunguza vihatarishi vya kisukari, uwezekano wa kupata ugonjwa wa kisukari kwao ni mdogo |  | Qn29 |
| 30. | Wewe una juhudi kidogo za kupunguza vihatarishi vya kisukari |  | Qn30 |
| 31. | Kama mtu ni tajiri na ni mnene kisha akapungua uzito ghafla na kuwa mwembamba ni ishara kuwa amefilisika |  | Qn31 |
| 32. | Kama mtu ni mnene, inabidi ahahakishe hapungui uzito wake la sivyo jamii inaweza kumdhania kuwa ameathirika na UKIMWI |  | Qn32 |
| 33. | Kuwa mwembamba siyo vizuri kwani watu watakuona kuwa wewe ni muadhirika wa VVU. |  | Qn33 |
| 34. | Gilasi ya juisi ya matunda ambayo haijawekewa sukari ni bora kuliko kutafuna matunda |  | Qn34 |
| 35. | Ni vigumu sana kwako kujizuia kula ikiwa chakula kitamu kipo cha kutosha |  | Qn35 |
| 36. | Ikiwa chumvi ni kwenye chakula au mboga ni vyema kuongeza wakati wa kula ili kutopoteza utamu wa chakula |  | Qn36 |

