2.6.4 Effectiveness of intervention package in reducing type2 diabetes risk factors: At the end of an intervention the mean comparison using independent T-test of all metabolic risk factors for T2DM will be made between the control and intervention groups. For pre-post analysis, the study will apply Generalized Linear Mixed Models (GLMM) to accommodate fixed and random variables. Sensitivity analysis will be conducted to assess if variables which will be statistically significant by GLMM model, will be consistently significant using the Bayesian Modelling technique with Markov Chain Monte Carlo (MCMC). Post and baseline analysis will also employ both linear and logistic regression to assess the factors associated with both primary and secondary outcome of interest. The following are the metabolic risk factors which will be assessed: High Density Lipoprotein Cholesterol (HDL-C), Low Density Lipoprotein Cholesterol (LDL-C), Total Cholesterol (TC), and triglycerides Cholesterol (TG-C) Body mass index (BMI), Waist Hips Ratio (WHR) and Blood Pressure (BP) (4,5,22,23,47,49), these will be our primary outcome of interest. The study will also assess mean knowledge and attitude scores as our secondary outcomes, mean days of fruits/vegetable consumption per week, mean number of cigarettes smoked per week, drinks consumed per week and mean MET/week between the control and intervention sites. Frequency of alcohol consumption and smoking will be also compared between the control and intervention sites. Lastly, the study will also compare the proportion of quitting alcohol consumption and smoking tobacco products between the control and intervention sites.

2.6.5 Develop a model for predicting metabolic risk factors for type2 diabetes: After collecting the endline data then a model will be developed using Multivariate/Joint Bayesian techniques to assess socio-economic and behavirioal risk factors which influence each metabolic risk factors and those which influence these factors jointly. **Table 4** below shows the type of predictive/explanatory factors which will be modelled per each metabolic risk factor of T2DM(16).

Table 4 Dependent and independent variables

| **Dependent variables- Metabolic Risk factors of T2DM** | **Independent variables/confounders** |
| --- | --- |

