**Section D: Step 1: Knowledge on type2 diabetes**

**Note: *This is a survey, not a test. Your answers will help identify which dietary advice people finding confusing. Therefore, if you do not know the answer, say `not sure/DK' rather than guess.***

| **Q-Number** | | **Question** | **Response** | **Code** |
| --- | --- | --- | --- | --- |
| *T2DM: Risk factors, symptoms, preventions strategies, complications Specific dietary related prevention strategies, nutritional values of foods and disease related with poor eating habits* | | | | |
| 37. | Have you had about diabetes? 1. Yes 2. No | |  | Qn37 |
| 38. | **If yes; mention at least five the risk factors of diabetes** | |  |  |
|  | 1. Age (40+ years) | |  | Qn38a |
|  | 1. Physical inactivity | |  | Qn38b |
|  | 1. Raised blood glucose | |  | Qn38c |
|  | 1. Raised cholesterol | |  | Qn38d |
|  | 1. Unhealthy eating | |  | Qn38e |
|  | 1. Family history of diabetes | |  | Qn38f |
|  | 1. Raised blood pressure | |  | Qn38g |
|  | 1. Alcohol consumption | |  | Qn38h |
|  | 1. Smoking | |  | Qn38i |
|  | 1. Excessive body weight | |  | Qn38j |
|  | 1. Gestational diabetes | |  | Qn38k |
|  | 1. Depression/stress | |  | Qn38l |
|  | 1. Others (specify)_______________________________ | |  | Qn38m |
| 39. | **Mention at least five symptoms of diabetes** | |  |  |
|  | 1. Extreme hunger | |  | Qn39a |
|  | 1. Frequent thirst | |  | Qn39b |
|  | 1. Frequent urination | |  | Qn39c |
|  | 1. Extreme weight loss | |  | Qn39d |
|  | 1. Blurred vision | |  | Qn39e |
|  | 1. Fatigue | |  | Qn39f |
|  | 1. Dry mouth | |  | Qn39g |
|  | 1. Dry or itchy skin | |  | Qn39h |
|  | 1. Poor wound healing | |  | Qn39i |
|  | 1. Extreme hunger | |  | Qn39j |
|  | 1. Frequent thirst | |  | Qn39k |
|  | 1. Others (specify)_______________________ | |  | Qn39l |
| 40. | **Mention at least five strategies for preventing type two diabetes** | | |  |
|  | 1. Control excessive body weight | |  | Qn40a |
|  | 1. Healthy eating habit | |  | Qn40b |
|  | 1. Control blood pressure | |  | Qn40c |
|  | 1. Healthy eating habit | |  | Qn40d |
|  | 1. Being physical active | |  | Qn40e |
|  | 1. Control blood glucose | |  | Qn40f |
|  | 1. Control blood cholesterol | |  | Qn40g |
|  | 1. Avoid excessive alcohol drinking | |  | Qn40h |
|  | 1. Avoid stress/depression | |  | Qn40i |
|  | 1. Quit smoking | |  | Qn40j |
|  | 1. Treat raised blood glucose during pregnancy | |  | Qn40k |

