**Sehemu D: Step 1: Uelewa kuhusu ugonjwa wa kisukari**

**Kumbuka**: Huuni utafiti, si mtihani. Majibu yako yatasaidia kutambua changamoto zilizopo katika jamii kuhusu ulaji bora. Kwa hiyo, kama hujui jibu, sema "sina na uhakika / Sijui" badala ya kubahatisha majibu.

| **Namba ya swali** | **Swali** | **Jibu** | **Code** |
| --- | --- | --- | --- |
| **Kisukari cha aina ya pili**: Vihatarishi, dalili, mikakati ya kuzuia, madhara ya kisukari, chakula bora, na magonjwa yasiyoambukiza yanayoambatana na ulaji usiozingatia afya. | | | |
| 37. | Umeishasikia kuhusu ugonjwa wa kisukari   1. Ndiyo 2.Hapana |  | Qn37 |
| 38. | **Kama jibu ni ndiyo, taja anagalau vihatarishi vitano vya ugonjwa wa kisukari.** |  |  |
|  | 1. Umri (Miaka 40 na kuendelea) |  | Qn38a |
|  | 1. Kutoshughulisha mwilia |  | Qn38b |
|  | 1. Kuongezeka sukari ndani ya damu |  | Qn38c |
|  | 1. Kuongezeka kwa mafuta kwenye damu |  | Qn38d |
|  | 1. Ulaji usiozingatia afya |  | Qn38e |
|  | 1. Historia ya kisukari ndani ya familia |  | Qn38f |
|  | 1. Shinikizo la damu la juu |  | Qn38g |
|  | 1. Unywaji wa pombe |  | Qn38h |
|  | 1. Uvutaji wa tumbaku |  | Qn38i |
|  | 1. Uzito wa juu |  | Qn38j |
|  | 1. Kuwa na kisukari wakati wa ujauzito |  | Qn38k |
|  | 1. Msongo wa mawazo |  | Qn38l |
|  | 1. Nyingine (taja)_______________________________ |  | Qn38m |
| 39. | **Taja angalau dalili 5 za kisukari** |  |  |
|  | 1. Njaa ya mara kwa mara |  | Qn39a |
|  | 1. Kiu ya mara kwa mara |  | Qn39b |
|  | 1. Kukojoa mara kwa mara hasa usiku |  | Qn39c |
|  | 1. Kupungua uzito ghafla |  | Qn39d |
|  | 1. Kutoona vizuri (upofu) |  | Qn39e |
|  | 1. Uchovu |  | Qn39f |
|  | 1. Midomo mikavu |  | Qn39g |
|  | 1. Ngozi kukauka na kuwasha |  | Qn39h |
|  | 1. Vidonda visivyopona haraka |  | Qn39i |
|  | 1. Others (specify)_______________________ |  | Qn39j |
| 40. | **Taja njia/mikakati 5 ya kuzuia ugongwa wa kisukari cha aina ya pili** | |  |
|  | 1. Kudhibiti uzito wa mwili |  | Qn39l |
|  | 1. Ulaji unaozingatia afya |  |  |
|  | 1. Kudhibiti shinikizo la damu |  | Qn40a |
|  | 1. Ulaji unaozingatia afya |  | Qn40b |
|  | 1. Kushughulisha mwili |  | Qn40c |
|  | 1. Kudhibiti kiwango cha sukari kwenye damu |  | Qn40d |
|  | 1. Kudhibiti kiwango cha mafuta kwenye damu |  | Qn40e |
|  | 1. Unywaji pombe unaozingatia afya |  | Qn40f |
|  | 1. Kuepuka msongo wa mawazo |  | Qn40g |
|  | 1. Kuacha kuvuta sigara |  | Qn40h |
|  | 1. Kutibu kiwango cha sukari wakati wa ujauzito |  | Qn40i |

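### The attitude statements come before the diabetes awareness filter and give away some answers to the risk-factor and prevention recall items, so consumer knowledge levels are biased upward

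*Protocol*

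**What the plan says.** Appendix B prints two consecutive blocks, both labelled Section D (Sehemu D in Swahili). The first holds 15 attitude statements, Qn22-36. The second is the knowledge block, Qn37-56. The order is the same in both languages.

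- **Qn22**, Swahili attitude block: "Inawezekana kuzuia kisukari cha aina ya pili kwa ulaji unaozingatia afya". One of the coded prevention answers under Qn40 is "Ulaji unaozingatia afya".
- **Qn27**, Swahili attitude block, contains "kuwa na historia ya kisukari ndani ya familia". One of the coded risk-factor answers under Qn38 is "Historia ya kisukari ndani ya familia". Qn23 also names family history.
- **Qn24** says that obesity raises the risk of diabetes. Excess body weight is a coded answer to Qn38.
- **Qn37** then asks whether the person has heard of diabetes: "Umeishasikia kuhusu ugonjwa wa kisukari".
- **Qn38** follows for those who say yes: "Kama jibu ni ndiyo, taja anagalau vihatarishi vitano vya ugonjwa wa kisukari". In English the task is "mention at least five the risk factors of diabetes".

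Section 2.6.4 lists "mean knowledge and attitude scores as our secondary outcomes", compared between control and intervention sites. Section 2.8 makes the share of respondents with high knowledge, before and after the intervention, a target indicator. Consumer knowledge also serves Objective 2 (section 1.5.2), planned paper 2 (section 2.12) and the explanatory factors in Table 4.

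**The concern.** A recall item measures what a person can produce unaided. If the same interview has just supplied some of the answers, part of what is recorded is repetition. The awareness question has the same problem: a person who has just responded to several statements about diabetes is unlikely to say they have never heard of it. Qn37 also opens the way to Qn38, so a prompted yes brings more people into the recall task.

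Most exposed are the descriptive results. Objective 2 and paper 2 report a level, and using one form in both arms does not remove bias from a level. The between-arm and before-after contrasts might also be affected, but that needs a further assumption, examined below.

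**Working it through.** The plan states no figure on this point, so there is none to reproduce. The check matches each attitude statement to the coded answers of Qn38-41 and then illustrates the size.

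**Step 1: count the distinct coded answers** (leaving out the open category and repeated rows). Qn38 has 12, Qn39 has 9, Qn40 has 10 and Qn41 has 7. Total 12 + 9 + 10 + 7 = 38.

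**Step 2: match the statements to the answers.**

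| Recall item | Given outright | Hinted only | Widest count |
| --- | --- | --- | --- |
| Qn38 risk factors | family history (Qn23, Qn27); excess weight (Qn24) | age (Qn26), inactivity (Qn25), unhealthy eating (Qn22) | 5 of 12 |
| Qn39 symptoms | none | none | 0 of 9 |
| Qn40 prevention | healthy eating (Qn22) | exercise (Qn25), weight control (Qn24) | 3 of 10 |
| Qn41 complications | none | none | 0 of 7 |
| Total | 3 of 38 (8%) | 5 more | 8 of 38 (21%) |

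**Step 3: awareness.** English statements 22, 23, 24, 26, 27, 28 and 29 name diabetes before Qn37, which makes seven. The Swahili Qn30 names it too, which makes eight.

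**Step 4: shift in the level.** Let k be the chance of naming an answer unaided, and c the chance that a person who would not have named it does so because of the cue. Then

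observed rate = k + (1 - k)c,

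and with m cued answers the mean count rises by m(1 - k)c. Neither k nor c is in the protocol; I assume k = 0.3 and c from 0.1 to 0.5. The uncued mean over Qn38-41 is 0.3 × 38 = 11.4 answers.

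- Outright cues only (m = 3): rise of 3 × 0.7 × 0.1 = 0.21 to 3 × 0.7 × 0.5 = 1.05.
- Widest count (m = 8): rise of 8 × 0.7 × 0.1 = 0.56 to 8 × 0.7 × 0.5 = 2.8.

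**Step 5: effect on a contrast.** If c is the same for two groups with unaided rates k1 and k2, the observed difference on a cued item is (k2 - k1)(1 - c). With equal true differences on all M items, the contrast in the count is multiplied by 1 - cm/M.

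| Items | Outright cues, c = 0.1 to 0.5 | Widest count, c = 0.1 to 0.5 |
| --- | --- | --- |
| Qn38-41 (M = 38) | 0.992 to 0.961 | 0.979 to 0.895 |
| Qn38 alone (M = 12) | 0.983 to 0.917 | 0.958 to 0.792 |
| Qn40 alone (M = 10) | 0.99 to 0.95 | 0.97 to 0.85 |

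Over Qn38-41 the loss is about 1-4% with the outright cues and 2-11% at the widest count. Adding Qn42-56 to a total score would dilute it further.

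**Step 6: the alternative model.** If the cue instead adds the same amount to every group's rate, the contrast is (k2 + a) - (k1 + a) = k2 - k1, and nothing is lost. The protocol does not settle which model applies.

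**The case against.** The best case on the other side is that little is given away and that it hardly touches the trial comparison. Much of this stands.

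- A reader might infer that the statements answer the whole recall block, or that five of 12 risk factors are handed over, exactly the number Qn38 asks for. The documents do not support this. Qn39 and Qn41 are not cued. Qn25 does not mention diabetes, Qn26 does not call age a cause, and Qn22 concerns prevention. In Swahili, Qn24 speaks of a large belly while the code speaks of high weight. Exact shared wording covers two phrases. No scoring rule is stated that would make five a full score.
- A reader might also infer that contrasts lose as much as the cue effect itself, for instance 20-60%. That applies an assumed cue effect to the cued items alone; it is not the loss on the score.
- Both arms and both rounds use the same form, so an additive effect cancels. This is right for contrasts and no answer for levels.
- That the statements are read aloud and the recall is unprompted is inferred. The form is filled in by an interviewer, and Qn70 has an instruction to read out the responses that Qn38-41 lack, so the inference is natural, but it is not printed.
- Nine further statements (Qn28-36) separate the cues from Qn37, and the knowledge block asks people to say they are unsure rather than guess. Both may weaken the cue. Neither removes it, since repeating something just heard is not guessing.
- Consent, with the study's aims, comes before the interview, so awareness is partly prompted in any order. This stands as a limit on what reordering can do for Qn37.

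**Conclusion.** The point holds in a limited form. The printed order cues Qn37, Qn38 and Qn40 in both languages, so consumer awareness and knowledge levels are biased upward. Three of 38 distinct recall answers are given outright and eight at most. Under the assumptions k = 0.3 and c = 0.1 to 0.5, the mean count over Qn38-41 rises by 0.2 to 1.1 answers with the outright cues and by 0.6 to 2.8 at the widest count.

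Shrinkage of the between-arm or before-after contrast is possible but not shown. It would be about 1-11% over Qn38-41, less in a total score, and only if the cue acts mainly on those who do not know.

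The metabolic primary outcomes and the sample size are unaffected. Vendor knowledge is outside the point, because section 2.6 assesses it through focus groups. The change is worth making because the bias falls on a stated objective and is cheap to reduce.

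**What to change.** In both language versions, before baseline:

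1. Ask Qn37-41 first, with a printed instruction to interviewers not to read the answer list.
2. Then ask the attitude statements Qn22-36.
3. Then ask Qn42-56.
4. Keep this order at baseline and endline in both arms.

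Give the attitude statements to everyone. Restricting them to people who answer yes to Qn37 would make a secondary outcome depend on awareness that the education itself can change. Leave Qn42-56 after the attitude statements, because their items on diet, salt and disease could prompt the attitude answers.

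The cost is reordering printed blocks and adding one instruction; no item is added. A small downside is that the open questions may slightly prime the attitude statements. If baseline has already been collected with the printed order, keep that order at endline so the rounds stay comparable, and report awareness, Qn38 and Qn40 levels as prompted.

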2.6 Material and method for each specific objective: A tool for data collection have been adopted from WHO STEP Survey questionnaire and other studies on similar topic(14,45–51). This tool will be then translated from English to Swhaili version. A tool also will consist of information including socio-demographic, behavioural, physical measurements and biological tests. A total of three focus group discussion (FGDs) involving street food vendors and six in-depth interviews with key stake holders will be conducted to assess their level of knowledge on type2 diabetes and hypertension risk factors and factors associated with adoption of food plate model and education package. Eight in-depth interviews will be conducted among public staff responsible with setting enabling and regulating working environment of food vendors. A three days training will be made to research assistants, this will involves orienting them on the study protocol, data collection tools and study ethics. **Table 3** shows the inclusion and exclusion criteria.

Table 3 Inclusion and exclusion criteria

| **Type of respondent** | **Inclusion** | **Exclusion** |
| --- | --- | --- |
| Street Food consumers | 1. Consuming at least three lunches meals/week to the same street food vendor (SFV) 2. Willing to participate in the study 3. Will remain in the study area for the duration of at least six months 4. Aged 25-64 years | Pregnant or lactating mothers |
| Street food vendors | 1. Vending food in the current site for not less than 6 months 2. Has at least 10 clients who have been consuming a least three lunch meals per week for not less than three months 3. Ready to implement the components required for an intervention model 4. Will remain vending food at same site for not less than six months 5. Aged 18 and above years | Not providing services daily |

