2.7.2 Plate Model: Before implementing the food plate model the consumers and vendors who will consent to be recruited for the intervention arm will be educated on how to prepare the standard and recommended food plate model and its hypothesized role of reducing metabolic risk factors of T2DM. We envisaged that knowledge about the current topic will influence practice and increase uptake of an intervention. The benefits of serving the food plate model will be explained to the vendors and these benefits will include serving small amount of carbohydrate, getting extra business by selling separate portion of vegetables and fruits after the project implementation thus getting more profit. For the consumers the benefits of plate model will include paying reduced price for carbohydrate since amount to be served will be the quarter of the normal served amount. Other advantages will include preventing the consumers from excess weight gain and contributing to balancing lipid T2DM metabolic risk factors. More emphasize will be given to the participants regarding the recommended ratio of fruits, vegetables, fats/protein and carbohydrate. Participants will be also instructed on how to ensure that the food plate model contain the recommended amount of potassium, magnesium and calcium levels. The food plate model will consists of more fruits and vegetables which will be half normal eaten plate before the intervention and each quarter will comprise carbohydrate and fats/protein. The participants will be insisted to avoid diary with high saturated fats and cholesterol.

2.8 Project monitoring: To ensure sustainability of the outcomes; the project will involve municipals officers during the implementation of the study so that they take lead in promoting supply and consumption of healthy diet. Intervention program will take three months(57). Monitoring will be done to ensure adherence and compliance as per study protocol requirements. This will involve signing a daily healthy plate form and weekly visits (intervention arm) while a daily lunch form and weekly visit (control arm). The main targets indicators will include mean of metabolic components (systolic and diastolic blood pressure, fasting blood glucose, body mass index, waist circumference, triglycerides and high density lipoprotein), proportion of respondents with high knowledge and positive attitude before and after intervention.

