**Section D: Step 1: Attitudes towards living healthy life to prevent type2 diabetes**

| **Q-Number** | **Question** | **Response** | **Code** |
| --- | --- | --- | --- |
|  | **Statements** | 1.Strogly agree  2.Agree  3.Disagree  4.Strongly disagree |  |
| 22. | It is possible to prevent diabetes by dietary management |  | Qn22 |
| 23. | Family history of diabetes influences to follow disciplined life |  | Qn23 |
| 24. | Obesity increases the risk of diabetes |  | Qn24 |
| 25. | Regular exercise needs lots of effort |  | Qn25 |
| 26. | Everybody should be aware regarding prevention of diabetes with increasing age |  | Qn26 |
| 27. | If there is increased chance of getting diabetes e.g. having family history then there is nothing to do to prevent or delay occurrences of the disease. |  | Qn27 |
| 28. | If you try you can reduce the risk of diabetes |  | Qn28 |
| 29. | People who take steps to reduce the risk factors of diabetes, their possibility of occurring diabetes is less |  | Qn29 |
| 30. | You have little control on your health risk |  | Qn30 |
| 31. | If a person is rich and fat if the suddenly becomes thin and slender is a sign of running bankrupt |  | Qn31 |
| 32. | If somebody is fat has to maintain his/her body structure otherwise can be considered to be HIV positive |  | Qn32 |
| 33. | To become thin and slender is not good because people will consider one to be HIV positive |  | Qn33 |
| 34. | A glass of unsweeted juice is better than chewing the actual fruits |  | Qn34 |
| 35. | It is very difficult to yourself to avoind overfeeding if delicious foods are prently available |  | Qn35 |
| 36. | If salt is low teste low in foods it is better to add when you are eating in order to maintan the food teste |  | Qn36 |

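### Swahili attitude item Qn30 asks about the respondent's effort where the English item asks about perceived control, so that item may not measure the attitude intended for a secondary outcome

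*Protocol*

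**What the plan says.** Protocol Section 2.6 states of the questionnaire: "This tool will be then translated from English to Swhaili version". Both versions are printed in Appendix B. The attitude section has 15 statements, Qn22 to Qn36, each answered on a four-point agreement scale.

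- **Qn30, English (Section D, attitudes):** "You have little control on your health risk"
- **Qn30, Swahili (Sehemu D, Mtazamo):** "Wewe una juhudi kidogo za kupunguza vihatarishi vya kisukari"
- **Qn36, English:** "If salt is low teste low in foods it is better to add when you are eating", followed by a clause about keeping the taste.
- **Qn36, Swahili:** "Ikiwa chumvi ni kwenye chakula au mboga ni vyema kuongeza wakati wa kula ili kutopoteza utamu wa chakula"

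The answers have two stated uses. Section 2.6.4 says: "The study will also assess mean knowledge and attitude scores as our secondary outcomes", with comparison between control and intervention sites. Section 2.8 lists among the main target indicators the "proportion of respondents with high knowledge and positive attitude before and after intervention". The protocol does not say which items enter the attitude score, how each is keyed, or what counts as a positive attitude.

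**The concern.** English Qn30 is a belief item: does the respondent think that health risk lies within his or her control? Swahili Qn30 is a self-report of behaviour, and its object narrows from health risk in general to diabetes risk factors. A belief and a report of one's own conduct can differ in the same person, and education may move them differently.

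Interviews using the Swahili form would collect the second quantity under the label of the first. If the item is then keyed from the English text, candour about low effort is recorded as an unfavourable attitude. What is at stake is the content validity of part of a secondary outcome and of a target indicator. The metabolic outcomes named in hypothesis 1 are not touched.

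In Swahili Qn36 the condition that the food is short of salt has dropped out, leaving an incomplete sentence.

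**Working it through.** No figure in the protocol has to be reproduced. The check is a comparison of wording, with the form's own vocabulary used to test the reading of the Swahili.

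**1. What the key word in Qn30 means on this form.** Swahili Qn25, in the same table, uses *juhudi* where the English has effort. For control, Swahili Qn40 repeatedly uses *kudhibiti* (body weight, blood pressure, blood glucose, blood cholesterol). So the form has a word for control, and Qn30 uses the word for effort instead.

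**2. How the two versions sort respondents.**

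| Belief | Own effort | English Qn30 | Swahili Qn30 |
| --- | --- | --- | --- |
| Risk can be controlled | High | Disagree | Disagree |
| Risk can be controlled | Low | Disagree | Agree |
| Risk cannot be controlled | High | Agree | Disagree |
| Risk cannot be controlled | Low | Agree | Agree |

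The versions give opposite answers in the second and third rows.

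**3. Consistency within the scale.** Qn28 says that trying can reduce the risk of diabetes. In English, agreeing with Qn28 and agreeing with Qn30 pull in opposite directions. In Swahili a respondent can agree with both without contradiction: risk can be reduced, and I do little about it.

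**4. Qn36.** The English is conditional on low salt; the Swahili has no word for low. In both versions agreement endorses adding salt while eating for the sake of taste, so topic and direction are kept.

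**5. Share of the score.** If all 15 items count equally (an assumption), Qn30 is 1/15 = 6.7% of the score.

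**6. Possible effect on the between-arm difference.** Assume that the other 14 items shift equally, that Qn30 shifts r times as much in the scored direction, and that the score's SD is unchanged. The standardised difference is then multiplied by (14 + r)/15:

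- r = 0 (no shift): 14/15 = 0.933. Squared, 0.871, the equivalent share of the sample.
- r = 0.5: 14.5/15 = 0.967. Squared, 0.934.
- r = 1 (same shift as the rest): 15/15 = 1, no loss.
- r below 0 (shift the wrong way): a larger loss. r above 1: an inflated difference.

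The protocol gives no basis for choosing r. Education might make participants more candid about low effort, so that they agree more. It might instead raise their effort, so that they agree less, which would be scored as favourable.

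**The case against.** **Scoring is not specified.** With no item list, key or cut-off, the place of Qn30 in the score is inferred from its position under the attitude heading. This stands, and the conclusion is conditional on it. The wording itself, however, is fixed in the protocol's appendix. An analysis plan could drop the item later but could not recover the answer to the English question.

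**The same form serves both arms.** A reader might infer that the attitude difference is therefore understated, or that people near the threshold for a positive attitude are misclassified. The documents support neither. The common form gives no clear directional bias, either sign of shift is plausible, and no threshold is stated.

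**Qn36 is not a different question.** A reader might count two failed items, obtain 13/15 = 0.87 (0.75 when squared), and conclude that a quarter of the effective sample is lost for this outcome. That requires no shift at all in Qn36, which is implausible when its direction is intact. The taste clause still suggests under-salted food, Swahili Qn82 asks about adding salt with the condition spelled out, interviewers receive three days of training, and the English Qn36 is itself garbled. Qn36 is a dropped word and no more.

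**Perceived control is covered elsewhere.** Qn27, Qn28 and Qn29 address whether risk can be reduced, and Qn35 is already self-referring in English. This is fair: one mistranslated item does not undo the scale. It does not make Qn30 correct.

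**Conclusion.** The mismatch in Qn30 is real and can be shown from the form's own vocabulary. The Swahili item measures self-reported effort; the English item measures perceived control. If Qn30 enters the attitude score keyed as the English implies, one item in 15 does not measure the intended attitude. The effect on the between-arm comparison cannot be signed or sized from the protocol; the illustrative factors above only show how it would vary with an unknown shift. Qn36 is a lesser fault.

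The point is minor in reach: part of one secondary outcome and one target indicator. It is still worth acting on, because correction before fielding costs almost nothing. It is also separate from a larger defect in the same Swahili table, where response option 4 repeats option 1 (strongly agree) although the English has strongly disagree. That slip affects all 15 items, and repairing it would leave Qn30 asking the wrong question.

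**What to change.** Before baseline:

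- Reword Swahili Qn30 as a statement on control, for example *Una uwezo mdogo wa kudhibiti hatari za afya yako*.
- In Swahili Qn36, insert *kidogo* after *ni*, so that the condition of low salt is restored.
- Check both items against the English by back-translation.
- Make these changes in the same correction that repairs response option 4.

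The cost is two lines in the Swahili form and a short back-translation.

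If data already exist with the printed wording, leave Qn30 out of the attitude score at both visits, or report the score with and without it. Keep Qn36, which still carries usable information on adding salt. The cost is a score of 14 items instead of 15. The wording should not be changed between baseline and end line while the item stays in the score, since the two visits would then not be comparable on it.
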